
### Procedure

To determine eligibility, potential participants complete an intake interview with a clinical psychologist prior to enrolment in the trial. All enrolled participants will complete assessments at preintervention (0 weeks), postintervention (8 weeks) and at 1 month following the completion of the intervention (12 weeks). Self-report assessments can be completed at home or on the phone with a member of the research team. In-person assessments are taken by the programme facilitator immediately prior to the first session and immediately following the final session. Detailed information about the methodology and timing of assessments is outlined in figure 1. Eligible participants will not have to pay for the Left Write Hook or boxing-only programmes. Left Write Hook is currently accessible in the community (delivered via a survivor-led charity) through a suggested ‘pay what you feel’ donation of up to AUD$450 to the Left Write Hook charity. Participants also receive a AUD$20 Giftpay voucher for each of the three online assessments they complete. Those in the boxing-only condition will be offered participation in the Left Write Hook programme at the end of the trial.

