### Sample size

A sample size of 128 participants (64 participants per arm, clustered into eight groups per intervention arm) would be required to have 80% power to demonstrate superiority of the Left Write Hook over the boxing-only intervention in terms of the primary effectiveness outcome of self-efficacy with a two-sided 5% significance level. This sample size is based on the following assumptions: clinically meaningful absolute treatment difference in mean change from preintervention to postintervention in self-efficacy score of 3 in favour of Left Write Hook (increase), a SD of 5.6 equal in each arm and at each time point (preintervention and postintervention)^70^ and an intraclass correlation of 0.02 to allow for possible clustering effects. Assuming a 15% dropout, a sample size of 150 participants is required (ie, 75 per arm clustered into 10 groups per intervention arm). This sample size represents 0.03% of the estimated number of gender-based violence survivors in the Melbourne population, based on Australian prevalence rates.^71^

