### Statistical analysis plan

Results will be analysed and reported as per the Consolidated Standards of Reporting Trials statement for cluster randomised trials.^72^ A detailed statistical analysis plan will be developed by study statistician/s prior to database lock. Analysis will follow on an intention-to-treat basis according to the cluster’s randomisation allocation. No interim analyses are planned. Cluster characteristics and participant characteristics at preintervention will be summarised using descriptive statistics.

The primary effectiveness estimand for Left Write Hook is defined according to the addendum to the International Council for Harmonisation (E9) Addendum on estimands in clinical trials.^73^ Left Write Hook aims to answer the specific research question: does implementation of the Left Write Hook programme, compared with boxing only, over 8 weeks, improve self-efficacy in survivors, as measured by the change in the General Self-Efficacy Scale,^53^ including the effect of the postrandomisation (intercurrent events) outlined below. Intercurrent events are events that occur postrandomisation and may preclude the observation of the outcome variable or affect its measurement.^74^ Intercurrent events will be tracked by the study team during the study. Possible intercurrent events include the following: participants not adhering to intervention protocol (not attending sessions altogether), participants withdrawing before the end of the intervention, change in or concurrent therapies and/or medication and hospitalisation. Primary estimand attributes are outlined in the online supplemental materials (Table S2).

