We will use linear mixed effects models to examine the change in the primary outcome of self-efficacy. The response variable will consist of preintervention and follow-up measures, and the model will include fixed effects for treatment group (intervention vs control) and the randomisation stratification factor (site). Random effects will be included to account for clustering at the participant and cluster levels. The absolute treatment difference in mean change from preintervention (week 0; baseline) to 8 weeks postrandomisation (ie, post-intervention) will be estimated with corresponding two-sided 95% CI and p value to evaluate the primary outcome. An adjusted treatment effect based on a model including potential confounding variables will also be obtained. Continuous secondary and exploratory outcomes will be analysed similarly to the primary outcome and targeting a similar primary estimand. Binary secondary and exploratory outcomes will be analysed using logistic regression with adjustment for site. Hair samples will be subject to mass spectrometry, with preintervention and postintervention differences analysed using paired sample t-tests. Quantitative data for the champion experience will be analysed descriptively only.

To determine implementation outcomes, qualitative data from semistructured interviews with participants, champions and peer facilitators will be analysed using NVivo, in line with reflexive thematic analysis.^75^ Themes will be interpreted in collaboration with the LEAG. Finally, the economic costs and benefits of Left Write Hook will be explored using Assessment of Quality of Life^76^ outcomes and costs of champion training and intervention delivery.

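### Under its usual reading, the participant random effect imposes one common correlation on weeks 0, 8 and 12, so the standard error of the week 0 to week 8 primary contrast can be wrong in either direction

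*Protocol article*

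**What the plan says.** The Statistical analysis plan section of the protocol article specifies a linear mixed model for self-efficacy. On the outcome vector it says: "The response variable will consist of preintervention and follow-up measures". On dependence it says: "Random effects will be included to account for clustering at the participant and cluster levels". It names no residual covariance and does not say whether the participant effect is an intercept only. The quantity of interest is "The absolute treatment difference in mean change from preintervention (week 0; baseline) to 8 weeks postrandomisation". Continuous secondary and exploratory outcomes are to be analysed in a similar way.

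The Procedure section sets the assessments at "preintervention (0 weeks), postintervention (8 weeks) and at 1 month following the completion of the intervention (12 weeks". The Maintenance section uses the effectiveness outcomes at 12 weeks. The Sample size section takes an SD of 5.6 at both preintervention and postintervention and gives no correlation between visits. Further detail is promised: "A detailed statistical analysis plan will be developed by study statistician/s prior to database lock".

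**The concern.** A random effect that accounts for clustering at the participant level is ordinarily a random intercept with independent residuals. With three visits in the model, that fits a single residual variance pooled over the pairs 0–8, 8–12 and 0–12. The target uses only the 0–8 pair, so pooling is harmless only if the average of the three pairs matches that one.

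The schedule gives reason to doubt it. Weeks 8 and 12 are four weeks apart with no programme sessions between them. Weeks 0 and 8 are eight weeks apart with the whole programme between them. A tight 8–12 pair pulls the pooled variance down, and a loose 0–12 pair pulls it up. At stake are the coverage of the primary confidence interval, the 5% test, and the same quantities for each continuous outcome measured at three visits. This concerns the covariance within participants only. It is separate from how the group-level effect is modelled, and it remains after visit and treatment-by-visit terms are in the model.

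**Working it through.** **Inputs from the article.** Difference 3 points, SD 5.6, two-sided 5% level, 80% power, cluster ICC 0.02, 64 evaluable per arm in eight groups (8 per group). Visits at weeks 0, 8 and 12.

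**The plan's own figure.** Per arm, 2 × (1.960 + 0.842)² × 5.6² / 3² = 54.7, so 55 (56 with the t distribution). The design effect is 1 + (8 − 1) × 0.02 = 1.14. This gives 55 × 1.14 = 62.7 or 56 × 1.14 = 63.8, which agrees with the stated 64.

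**What that implies for r(0,8).** The calculation uses 5.6 as the SD of the change score. With SD 5.6 at each visit, the SD of change is 5.6 × √(2(1 − r)), which equals 5.6 only when r = 0.5. I therefore take r(0,8) = 0.5. The other two correlations are assumptions.

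**Formula.** Take complete data, equal variances, a mean that is free in each arm at each visit, and no cluster effect. The estimate is then the difference in mean change. The random-intercept model puts its residual variance at s²(1 − r̄), where r̄ is the mean of the three pairwise correlations. The 0–8 contrast requires s²(1 − r(0,8)). Hence

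- SE ratio (model to true) = √[(1 − r̄) / (1 − r(0,8))]
- two-sided error rate = 2 × [1 − Φ(1.96 × ratio)]

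The ratio falls below 1 exactly when r(8,12) + r(0,12) > 2 × r(0,8).

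**Results with r(0,8) = 0.5.**

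| r(0,12) | r(8,12) | r̄ | SE ratio | Error rate |
|---|---|---|---|---|
| 0.50 | 0.50 | 0.500 | 1.000 | 5.0% |
| 0.50 | 0.60 | 0.533 | 0.966 | 5.8% |
| 0.50 | 0.70 | 0.567 | 0.931 | 6.8% |
| 0.50 | 0.80 | 0.600 | 0.894 | 8.0% |
| 0.45 | 0.70 | 0.550 | 0.949 | 6.3% |
| 0.354 | 0.707 | 0.520 | 0.980 | 5.5% |
| 0.30 | 0.70 | 0.500 | 1.000 | 5.0% |
| 0.35 | 0.60 | 0.483 | 1.017 | 4.6% |

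The row with 0.354 and 0.707 is pure decay with time: 0.5^(12/8) and 0.5^(4/8).

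**Unequal variances.** The model then averages the variances of the three pairwise differences. Take correlations 0.5, 0.45 and 0.7 for the pairs 0–8, 0–12 and 8–12, with SDs of 5.6, 5.6 and 6.6 at weeks 0, 8 and 12.

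- 0–8: 31.36
- 8–12: 31.36 + 43.56 − 2 × 0.7 × 36.96 = 23.18
- 0–12: 31.36 + 43.56 − 2 × 0.45 × 36.96 = 41.66

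The mean is 32.06 and the ratio is √(32.06 / 31.36) = 1.011. A larger week 12 SD has turned an understatement into a slight overstatement.

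**Simulation check.** I simulated 40,000 trials per row with 64 per arm and no cluster effect. Rejection rates under the random-intercept model were within about half a percentage point of the formula (for example 6.9% and 8.1% for the 6.8% and 8.0% rows). Using the variance of the 0–8 change itself, which is what an unstructured covariance delivers with complete data, the rates were 4.9% to 5.3% throughout.

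**The case against.** The strongest reply is that the article does not state the model computed above. It does not say intercept only or independent residuals, and it does not name week 12 as part of the primary model. It defers detail to an analysis plan, where covariance structure is often settled. The list of fixed effects has no visit terms, so the calculation already completes that list while reading the random-effects sentence as complete. The correlations are assumed. The scenarios with the largest error keep r(0,12) equal to r(0,8), although the 12-week gap is longer. Consistent decay with time gives only 5.5%.

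Most of this stands as a limit on the claim. A reader might infer that the primary interval will be too narrow, or that weeks 8 and 12 being more alike is enough to make it so. The documents support neither. Closer resemblance of weeks 8 and 12 is not sufficient, because r(0,12) and the variances also decide the direction, and some of the cases above show no error or a conservative test. Nor is it right to say that the text forces a common correlation, since a random slope or a structured residual covariance is not ruled out.

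What the reply does not remove is that the article makes a choice: within-participant dependence is handled by a random effect, described in the same terms as the group effect. An intercept is its ordinary meaning. A participant intercept cannot simply be supplemented with a free 3×3 residual matrix, because the two are not separately identified with three visits. An unstructured covariance therefore replaces the stated participant term.

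**Conclusion.** The point holds conditionally. If the participant term is a random intercept with independent residuals and all three visits enter, the model-based standard error of the primary contrast is right only by coincidence of the correlations and variances. In the scenarios tabulated it ranges from about 11% too small to about 2% too large, with error rates of about 8.0% down to 4.6%. These are the cases tried and not bounds. Understatement is the more plausible direction given the schedule, but the documents do not establish it. If only weeks 0 and 8 enter, there is one correlation and this problem does not arise.

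The figures rest on r(0,8) = 0.5, on assumed values for the other two correlations, on complete data and on no cluster effect. The 15% dropout and ICC of 0.02 that the article plans for are not in them. Severity is minor to moderate: the error is modest and conditional, but it bears on the primary interval and is easily avoided.

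**What to change.** State the within-participant covariance explicitly. Replace the participant random intercept with an unstructured residual covariance over weeks 0, 8 and 12, keep the cluster-level random term, and estimate the week 8 difference in change from that model. Alternatively, fit the primary model to weeks 0 and 8 only. Apply the same choice to the continuous secondary and exploratory outcomes measured at three visits.

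The unstructured form does not depend on which way the correlations fall, so the question of direction need not be settled first. The cost is one line of wording in the analysis plan and six within-participant covariance parameters in place of two, estimated from up to 150 × 3 = 450 scores. No new data are needed.

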## Methods

### Study design

This is a Type II hybrid effectiveness-implementation two-arm cluster-randomised controlled trial comparing Left Write Hook (intervention) to trauma-informed non-contact boxing-only (control). The primary effectiveness outcome measure will be self-efficacy at the primary endpoint of postintervention (8 weeks). Alongside the Left Write Hook programme, we aim to concurrently assess the implementation of ‘champion training’, a Trauma-Informed Writing and Boxing Facilitation programme for new Left Write Hook facilitators. The primary implementation outcome will be fidelity of intervention training and delivery of both the Left Write Hook and the boxing-only conditions within the trial, across different facilitators and sites. Fidelity refers to the degree to which an intervention or programme is delivered as intended.^60^ A hybrid trial design is appropriate for our research as it evaluates both effectiveness and implementation outcomes, accelerating the potential for broader implementation.^63^

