#### Active control: boxing-only

Participants randomised to control will complete 8× weekly group sessions of trauma-informed non-contact boxing, without writing and without a specific focus on empowerment, to control for the positive effects of exercise on self-efficacy. Each week, participants will complete a 45-min group boxing session, led by a boxing instructor (ie, intervention is not peer-led) at the same sites as the intervention arm. This replicates the type of trauma-informed exercise class that survivors could access in their local community. Boxing was selected as the exercise modality based on consumer input that identified it as the most acceptable exercise option for an active control, particularly in the context of consenting to randomisation. The control group therefore represents trauma-informed exercise options as usual, without three unique components of the Left Write Hook intervention: the peer-led nature of intervention, expressive writing and the focus on empowerment that links from the expressive writing to the trauma-informed non-contact boxing component to encourage expression through physical movement. Trauma-informed considerations for the boxing-only group are outlined in table 2.

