#### Effectiveness

Evaluation of effectiveness will be conducted at the individual level (participant and facilitator, including withdrawals) to determine the impact of the programme on psychosocial and physical health outcomes. Participants who withdraw from the study will still be invited to complete outcome measures. All outcome measures are outlined in the online supplemental materials (Table S1). The primary effectiveness outcome is self-efficacy, measured by participant score on the General Self-Efficacy Scale.^53^ Secondary effectiveness outcomes will include complex PTSD symptoms, trauma-related cognition (trauma memory quality and post-traumatic cognitions) and indices of physical health (strength, flexibility, aerobic fitness and balance). Exploratory effectiveness outcomes include depression and anxiety, social connectedness, mental well-being, quality of life, health behaviours (exercise habits, smoking and vaping frequency, alcohol intake and use of health resources) and physical health (blood pressure, chronic pain, sleep quality and stress hormones). Self-report measures will be administered online via Qualtrics, either at home in a comfortable environment, via phone call with a member of the research team or at the gym/sports centre with the support of a facilitator. Due to logistical constraints, preintervention in-person assessments (physical fitness, blood pressure and hair sample) will be completed immediately prior to the commencement of the first Left Write Hook or boxing sessions at the sport centre by an unmasked programme facilitator, with responses recorded via Qualtrics. Hair samples indexing stress hormones (see online supplemental Table S1 for details) will be collected by the programme facilitator, trained in collection procedure by a member of the research team. Samples will be wrapped in aluminium foil and stored in a plastic ziplock bag and kept at room temperature in a locked cabinet until analysis, as per recommendations in the field.^68^

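### Hair stress hormones are assigned a paired pre-post t-test, which makes no comparison between arms and conflicts with the plan's own rule for continuous exploratory outcomes

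*Protocol article*

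**What the plan says.** All references are to the protocol article.

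- **Status of the outcome.** The Effectiveness section places stress hormones among the exploratory effectiveness outcomes, under "physical health (blood pressure, chronic pain, sleep quality and stress hormones". Effectiveness evaluation is there "to determine the impact of the programme on psychosocial and physical health outcomes". Hair is the specimen, and the baseline sample is taken before the first session in both arms.
- **General rule.** The Statistical analysis plan section says: "Continuous secondary and exploratory outcomes will be analysed similarly to the primary outcome and targeting a similar primary estimand".
- **What that rule implies.** For the primary outcome the responses are the baseline and follow-up values, and "the model will include fixed effects for treatment group (intervention vs control) and the randomisation stratification factor (site". Also: "Random effects will be included to account for clustering at the participant and cluster levels". The quantity estimated is the difference between arms in mean change to 8 weeks.
- **What is said for hair.** Shortly afterwards, in the same paragraph: "Hair samples will be subject to mass spectrometry, with preintervention and postintervention differences analysed using paired sample t-tests".

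No other sentence in the article names an analysis specifically for hair hormones.

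**The concern.** The trial is a "two-arm cluster-randomised controlled trial comparing Left Write Hook (intervention) to trauma-informed non-contact boxing-only (control". Its evidence about the programme is the contrast between randomised arms. A paired t-test, whether run within each arm or on everyone pooled, tests whether average within-person change is zero. It does not estimate Left Write Hook against boxing-only, takes no account of site or group, and drops anyone who gave only one of the two samples.

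This matters because both arms box weekly for 8 weeks. The control was chosen "to control for the positive effects of exercise on self-efficacy". That reason is stated for self-efficacy, but a shared effect of exercise on a stress hormone is just as plausible. Any change common to both arms, from exercise or anything else, would give a small paired p-value although the writing, the peer leadership and the empowerment focus had added nothing. Reported as an effectiveness result, it could be read as a biological effect of the programme.

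**Working it through.** **1. The plan's own figure.** No figure is given for the hair analysis. The only numbers available are those in the Sample size section, for self-efficacy: difference 3, SD 5.6, two-sided 5%, 80% power, intraclass correlation (ICC) 0.02, eight groups and 64 participants per arm.

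- Per arm, unclustered: 2 × [5.6 × (1.960 + 0.842) / 3]² = 54.7.
- Design effect for groups of 8: 1 + (8 − 1) × 0.02 = 1.14.
- 54.7 × 1.14 = 62.4, so 63, or 64 as eight groups of eight. This agrees with the plan.
- Dropout: 128 / 0.85 = 150.6, so 151 against the stated 150, which is close enough.

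This takes 5.6 as the SD of the change, which equals the per-visit SD if the pre-post correlation is 0.5. The figures of 64 per arm, eight groups and ICC 0.02 are borrowed below as assumptions, because no hair-sample number or hormone ICC is given.

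**2. The two rules side by side.**

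| | Rule for continuous exploratory outcomes | Hair sentence |
|---|---|---|
| Arm term | Yes | None named |
| Site | Fixed effect | None named |
| Group (cluster) | Random effect | None named |
| Quantity tested | Difference between arms in change | Change against zero |
| Participant with one sample | Retained | Dropped |

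Stress hormones are a continuous exploratory outcome, so both columns apply to them.

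**3. What the paired test does when the arms do not differ.** Let both arms change by the same amount *c*, in units of the SD of the change. The values of *c* are assumptions.

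- One arm: noncentrality = *c* × √64 = 8*c*, giving 1.6, 2.4 and 4.0 for *c* = 0.2, 0.3 and 0.5.
- Pooled: *c* × √128 = 11.3*c*, giving 2.3, 3.4 and 5.7.

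A simulation added the clustering (20,000 trials per scenario, eight groups of eight per arm, ICC 0.02, true arm difference zero). A t-test on group mean changes stood in for the between-arm analysis. Percentage of trials significant at 5%:

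| Common change *c* | Paired, Left Write Hook arm | Paired, both arms pooled | Exactly one arm significant | Between-arm, group level |
|---|---|---|---|---|
| 0 | 6.7 | 6.6 | 12.7 | 4.9 |
| 0.2 | 36 | 61 | 46 | 4.9 |
| 0.25 | 51 | 79 | 50 | 4.9 |
| 0.3 | 65 | 91 | 46 | 4.7 |
| 0.5 | 97 | 100 | 6 | 5.2 |

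The between-arm test holds its nominal level throughout. The paired test responds to the common change, as it is built to do.

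**4. The part due to ignoring clustering.** With *c* = 0, the variance of the arm mean is 1.14 times what the paired test assumes. The rejection rate is about 2 × P(Z > 1.96 / √1.14) = 2 × P(Z > 1.84), or 6.6%, in line with the simulated 6.7%. This is small beside the lack of an arm contrast.

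**The case against.** The best defence is that the paired test is an addition. The general rule already gives every continuous exploratory outcome a between-arm model, stress hormones are on that list, and the hair sentence does not say that its test replaces the model. The article also commits to intention-to-treat analysis by cluster allocation, to cluster-trial reporting standards and to a fuller analysis plan before database lock.

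Part of this stands. A reader might infer that no between-arm analysis of hormones will be done, and the text does not prove that. But the hair sentence is the more specific of the two, names one test, and does not call it supplementary or descriptive. Nor is this detail left for later: the article fixes a test, and a later plan would have to overrule or reinterpret it. On either reading the sentences need reconciling.

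Three stronger inferences should be resisted.

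- **That half of such trials would show a spurious difference between arms.** The 50% figure for exactly one significant arm requires the authors to compare significance across two within-arm tests, which the article does not propose. It is also near its peak at 0.25 SD and falls to 6% at 0.5 SD.
- **That hormones are the only biological outcome.** Blood pressure is listed beside them, and the full table of measures is in supplementary material not shown here.
- **That ignoring clustering is a serious error in itself.** At the assumed ICC it moves 5% to 6.7%, and that ICC was stated for self-efficacy.

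**Conclusion.** The point holds. The test named for hair hormones does not address the randomised comparison, and it conflicts with the rule for continuous exploratory outcomes in the same section. With no true arm difference and a common change of 0.2 to 0.5 SD, the paired test in the Left Write Hook arm is significant in about 36% to 97% of trials, against about 5% for a between-arm analysis. Those percentages rest on assumed changes, 64 complete pairs per arm in groups of eight, and an ICC of 0.02; none of these is given for hormones. The lack of an arm contrast depends on none of them.

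The reach is limited. A reader might infer that the trial's main conclusions are at risk, but stress hormones are one of many exploratory outcomes and do not enter the stated hypothesis. The primary and secondary analyses and the sample size are unaffected. It should be corrected, but it is not critical to the trial.

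**What to change.** Replace the hair sentence so that hormone concentrations from mass spectrometry, log-transformed if skewed, are analysed with the linear mixed model already set for continuous outcomes: pre- and post-intervention values as the response, the between-arm difference in change (arm-by-time contrast) as the estimate, site as a fixed effect, and random effects for participant and cluster. Label any paired pre-post summary, by arm or pooled, as descriptive and not as evidence of effectiveness.

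Keeping both values in the response follows the plan's own model and retains participants with a single sample. A model of the 8-week value adjusted for baseline would be a further method for this one outcome and, without imputation, would lose those participants.

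The cost is one sentence. No new samples, visits or participants are needed. Recruitment is expected to run until June 2026 and the detailed analysis plan is due before database lock, so on the published timetable the change can be prespecified before the statisticians are unmasked.
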